#### Data, Safety, and Confidentiality

##### Data and Safety Monitoring Plan

A data and safety monitoring plan was developed and registered with the funding agency. We anticipate that the largest risk in this study is a breach of confidentiality. Breaches of confidentiality will be reported to the IRB, where action at the institutional level will take place. In addition, the study procedures will be stopped, and we will re-evaluate our procedures.

##### Potential Harms

Potential unexpected events include a breach in confidentiality, as some participants would not have disclosed their HIV status to their intimate partners, family members, or friends. Some participants may be sharing their mobile devices, and so a potential risk exists. Adverse events and serious adverse events may be reported spontaneously by the participant. If a potential adverse event is identified, the PI will report the adverse event directly to the IRB. Events that are psychosocial in nature and that meet the criteria for reporting to the IRB (unexpected, related, and serious) will be reported in the 10-day timeframe established. Other events will be reported annually.

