### Eligibility Criteria

The following are the eligibility criteria for the study: (1) women aged ≥18 years; (2) confirmed HIV diagnosis (per the clinic’s standard); (3) active patient (ie, not withdrawn, transferred, or dismissed); (4) 2 or more previously scheduled visits 12 months before the study enrollment; and (5) nonadherence, based on 1 or more of the following criteria: missed 1 or more visits, having a viral load >20 copies/mL, or not taking HIV antiretroviral medications as prescribed.

Participants will have to confirm at the time of enrollment that they possess a working mobile phone number (to receive text messages). We will exclude women with serious psychiatric diagnoses, who are cognitively impaired or are not able to consent for themselves.

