#### Texting System

For the mHealth system, participants will be prompted to respond to predefined responses such as “Press ‘1’ if you received this message” and “Press ‘2’ if you would like us to call you.” Downloadable data usage logs will track messages that are opened and the participants’ responses. Periodically, participants will receive text surveys regarding the usefulness of a message immediately upon opening the message. These data will further guide messaging development and gauge intervention adherence.

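### For confidentiality breaches through a participant's phone, the article states no detection method except spontaneous report, so a low or zero count would be hard to interpret

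*Protocol article*

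**What the plan says.** The Data and Safety Monitoring Plan section of the protocol article ranks the risks: "We anticipate that the largest risk in this study is a breach of confidentiality". It says breaches go to the IRB and adds: "In addition, the study procedures will be stopped, and we will re-evaluate our procedures". It also says that a separate data and safety monitoring plan was registered with the funder. That plan is not among the documents shown.

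The Potential Harms section links a breach to women who have not told partners, family or friends about their HIV status, and then to the phone: "Some participants may be sharing their mobile devices, and so a potential risk exists". On detection it says: "Adverse events and serious adverse events may be reported spontaneously by the participant". Reporting follows once an event is known: "If a potential adverse event is identified, the PI will report the adverse event directly to the IRB".

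Other sections bear on the point:

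- Eligibility Criteria asks for a working mobile number. It does not ask who else can open the phone.
- Table 1 lists the outcomes collected at T0, T1 and T2. None concerns adverse events or disclosure, and the Instrumentation section describes no such item.
- The Privacy and Security section keeps clinic names and terms such as HIV or AIDS out of the messages.
- The Texting System section offers a call-back code and says: "Downloadable data usage logs will track messages that are opened and the participants’ responses".
- Key informants from the intervention group (KI2) are interviewed after T1, and closing focus groups (FG2) are held after T2.

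**The concern.** The article sets out a risk, a route by which it could happen, a way of finding it, and consequences once it is found. For the phone route, the way of finding it does not match the risk. A woman whose partner or relative has learned something from a text may have good reason not to raise it unprompted. IRB reporting and the stop of procedures both need an identified event, so for this route they depend on her doing so.

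The stake is interpretation as much as safety. This is a feasibility and acceptability trial of texting, and unwanted disclosure is a harm that a later, larger trial will want to know about. If nobody is asked, a report of no events could mean that texting was safe in this clinic or that affected women stayed silent. The usage logs do not resolve this. According to the Data Preparation section they are matched to participants by mobile number, and an open on that number does not show who read the message.

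**Working it through.** The article states no event rate, detection rate or power figure, so there is none to reproduce. The question is how often a disclosure could occur without any report reaching the team.

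**Inputs from the article.** Target Sample Size gives about 20 women per language in three languages, half of them controls: 20 × 3 = 60. Assignment to Study Arms gives about 10 per language per arm: 10 × 3 = 30 per arm, and 2 × 30 = 60. The two agree, so n = 30 in the text arm.

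**Assumed inputs.** The article gives neither of these, so ranges are used:

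- p, the risk that a text-arm woman has an unwanted disclosure: 3%, 5%, 10%, 20%.
- s, the chance that an affected woman volunteers it: 25%, 50%, 75%.

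Women are treated as independent.

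**Formulas.** P(at least one disclosure) = 1 − (1 − p)^30. P(no report at all) = (1 − ps)^30. P(at least one disclosure and no report) = (1 − ps)^30 − (1 − p)^30. The subtraction removes the case in which silence is correct because nothing happened.

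**Example.** With p = 5% and s = 25%: (1 − 0.0125)^30 − 0.95^30 = 0.686 − 0.215 = 0.471.

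| p | At least one disclosure | Occurs, none reported: s = 25% | s = 50% | s = 75% |
|---|---|---|---|---|
| 3% | 60% | 40% | 23% | 10% |
| 5% | 79% | 47% | 25% | 10% |
| 10% | 96% | 43% | 17% | 5% |
| 20% | 99.9% | 21% | 4% | 1% |

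The range is 0.6% to 47%. Silence is plausible when events are few and volunteering is low, and becomes unlikely as either rises.

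**What a zero count would show.** With every event found, zero in 30 gives a one-sided 95% upper bound of 1 − 0.05^(1/30) = 9.5%. If only a fraction s is found, the bound applies to ps, so the bound on p is 9.5%/s: 12.7% at s = 75%, 19% at 50%, 38% at 25%. Since s is unknown, the bound is too.

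**With a direct question.** If asking found 90% of events (assumed), the chance that a disclosure occurs and none is found would be 3.9%, 3.7%, 1.7% and 0.1% for p = 3%, 5%, 10% and 20%. For example, at p = 10%: 0.91^30 − 0.90^30 = 0.059 − 0.042 = 0.017. The bound after a zero count would be 9.5%/0.9 = 10.6%.

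**The two safety sections side by side.** The Data and Safety Monitoring Plan section sends breaches to the IRB and stops procedures, with no condition attached. Potential Harms lists a breach among unexpected events, although the other section anticipates it as the largest risk. It gives the 10-day timeframe to psychosocial events that are unexpected, related and serious, and leaves other events to annual reporting. A breach that is anticipated or not serious could therefore be handled in two ways.

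**The case against.** The strongest reply is that the method of eliciting adverse events is normal content for the monitoring plan, which exists and is not shown. That stands, and it makes the point conditional. It does not remove it, because the article chose to state a method for this risk and the method it states is passive.

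A reader might infer more than the documents support:

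- **That spontaneous report is the trial's only detection route.** The article says events may be reported that way and excludes nothing. The named risk is a breach in general. The Confidentiality section also covers contact forms, record-number logs, recordings and cloud files, where staff could notice a breach themselves. The point is limited to the phone route.
- **That a text seen by someone else is an HIV disclosure.** Messages carry no clinic name and no HIV terms, and women choose the timing and content of medication reminders. Seeing a message is not a disclosure, although the article itself still says a risk exists.
- **That nobody would hear of an event.** The call-back code, KI2 and FG2 could surface some, and a team member is present when forms are completed. But call-back depends on the woman, KI2 involves 2 to 3 participants per language, FG2 involves 5 to 8 per language, and none of these is described as asking about harm.
- **That lapsed numbers keep receiving texts for months, or that there is no wrong-person code.** The section on personalization speaks of updating customizations, at T1, T2 or any time a woman chooses. The reply codes are given as examples. Neither inference is established.

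It is also fair to say that the probabilities rest on assumed rates and that no figure in the article is wrong.

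**Conclusion.** The point holds in a limited form. For breaches arising through a participant's phone, the article states one detection method, spontaneous report, and lists no measure at T1 or T2 that asks about them. Unless the monitoring plan already solicits such events, a low or zero count in about 30 text-arm women cannot be separated from non-reporting.

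The chance of an unreported disclosure is about 1% to 47% over the assumed ranges. That range shows the count would be hard to interpret. It does not predict that disclosures will occur or be missed. The change is worth making because it is cheap and because the article describes the texting system as still being designed and the intervention as not yet launched. The difference between the two safety sections does not depend on any assumption.

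**What to change.** First check the registered monitoring plan. If it already has staff ask about disclosure at set times, state this in the protocol and no new question is needed. Otherwise keep spontaneous reporting and add the following to existing contacts:

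1. At T0, record whether anyone else can open the participant's phone.
2. At T1 and T2, ask one fixed question: since the last visit, has anyone learned, through the study or its messages, something about you that you did not want known? Define in advance that the mere viewing of a message does not count as a disclosure.
3. Confirm the mobile number at the same visits.
4. Report disclosure events by shared-phone status alongside the acceptability results.

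Separately, reconcile the Data and Safety Monitoring Plan and Potential Harms sections on how a breach is classified, when it is reported and whether the stop of procedures is conditional. Which rule applies is for the investigator and the IRB to decide.

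The cost is a few form items at visits where a team member is already present, and an IRB amendment with wording in three languages. More events will be recorded than under spontaneous reporting alone, so the counts should be presented with the way they were collected.

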##### Confidentiality

A breach of confidentiality is still a possible risk, but measures will be taken to minimize this risk. The study team will have to collect names and contact information to schedule a participant for a focus group or contact as a key informant and conduct the chart review; therefore, complete anonymity is not possible.

Participants will be assigned an ID number, and only the ID number will identify the data collected on all questionnaires. The questionnaires will not be linked to the consent forms and contact information forms and will not record any identifying information such as name, date of birth, or contact information. The only protected health information that will be stored in the mHealth system is the participants’ cell phone numbers. No PHI will be transmitted to the participants. Only the study team members will have access to the data. A study log, which includes MRN, study identification number, and date consented, will be kept in an electronic file, secured with an encrypted password. Only the study team members will know the passwords. The contact information forms and recordings will be destroyed upon the completion of the study. The consent forms and logs will be destroyed after 3 years. The participants’ names or personal identifiers will never be transmitted or be part of the study publication of its findings.

The participants’ audio recordings, study records, and survey results will be kept private and will not be identified in any publication. Data will be presented in aggregate only. The completed questionnaires, contact information forms, consent forms, and recording devices will be kept in a locked cabinet in the office of the PI. The data collection form, along with the electronic files of the focus group and key informant recordings and their transcriptions will be stored in a university-approved HIPAA-compliant database and in cloud-based storage. Only the study team members will have access to the data. Data collection forms and transcriptions will be kept for analysis. The completed questionnaires will be destroyed after 3 years.

#### Research Ethics Approval

The PI obtained IRB approval to conduct the study. The IRB approved the study personnel, consent forms, recruitment materials, instruments, and all other materials given to the participants. Changes to the study protocol will be submitted in writing to the IRB, and only IRB-approved modifications will be implemented.

## Results

The study was funded in December 2018. IRB approval for the English language version of the protocol was attained in January 2019. As of March 2020, baseline quantitative data have been collected on 54 study participants (28 English speakers, 14 Spanish speakers, and 12 Haitian Creole speakers). The first 3 focus groups (1 in each of the 3 languages) have taken place, with a total of 20 participants. The findings from these data are currently being integrated into the design of beta version of the mHealth texting system.

## Discussion

### Overview

As of April 2020, 54 participants have been enrolled. Based on the number of subjects enrolled, we anticipate continued participation and enrollment, where we will further test the system and launch the intervention.

### Strengths and Limitations

The most significant strength of this study is that, to our knowledge, it is the first HIV adherence intervention in the United States that is designed for minority women across multiple cultural and linguistic contexts. We recognize that the most significant limitation of the study is that there may not be sufficient power to test complex interaction models for the quantitative arm of the analyses. Furthermore, because the intervention is being tested among a cohort of women with a history of nonadherence, study retention may be negatively impacted.

## Appendix

Multimedia Appendix 1 Peer review reports from Miami CTSI KL2 Awards FY19.

## Abbreviations

ANOVA: analysis of variance
CDRISC-25: Connor-Davidson Resilience scale
EMR: electronic medical record
HBM: Health Belief Model
HIPAA: Health Insurance Portability and Accountability Act
IRB: institutional review board
mHealth: mobile health
MRN: medical record number
PHI: personal health information
PI: principal investigator
STEP-AD: Striving Towards Empowerment and Medication Adherence
